## Abstract

**Background:**

Substance use is highly prevalent among children and adolescents in Chile, and it is known how it impacts their health and social adjustment. The call for effective prevention of substance use among children adolescents has resulted in numerous school-based programs, and particularly, the Social Competence Promotion Program among Young Adolescents (SCPP-YA) has been proved to be successful for promoting social and problem-solving skills in addition to preventing substance abuse in the US population. The purpose of this study is to test the effectiveness of the Social Competence Promotion Program among Young Adolescents (SCPP-YA) in Chile (“Mi Mejor Plan”).

**Methods:**

This is a cluster randomized controlled trial, parallel-group type, where “Mi Mejor Plan” is compared to standard school preventive curricula in control schools. A total of 10 schools and 600 adolescents are expected to be recruited and randomized with 1:1 allocation. During formative work, the SCPP-YA program was culturally adapted to Chile. The effectiveness of this program will be assessed using the European Drug Addiction Prevention Trial Questionnaire (EU-Dap), measuring substance use prevalence and risk and protective factors in baseline, post-intervention, and 4 months after the end of the intervention.

**Discussion:**

The proposed study will be the first to test the effectiveness of the Social Competence Promotion Program among Young Adolescents (SCPP-YA) in Chile in a cluster randomized control trial and also the first study evaluating this program in Spanish-speaking Latin America. SCPP-YA has been implemented successfully in the USA. Thus, if the effects of the program are positive, wide implementation in Chile and Latin American countries is possible soon.

**Trial registration:**

Clinical Trials NCT04236947. Registered on January 22, 2020.

## Administrative information

Note: the numbers in curly brackets in this protocol refer to SPIRIT checklist item numbers. The order of the items has been modified to group similar items (see http://www.equator-network.org/reporting-guidelines/spirit-2013-statement-defining-standard-protocol-items-for-clinical-trials/).

## Introduction

### Background and rationale {6a}

Adolescence is a particularly challenging stage during which young people must deal with their biological development and social demands from their peers, family, and environment. These demands often produce interpersonal stress and a variety of issues that make adolescents susceptible to emotional and behavioral problems [1]. Substance abuse is especially worrying due to its implications for personal health and social adjustment. For instance, marijuana use can increase the likelihood of respiratory issues [2]. Substance use has also been found to affect cognitive functioning, with users of tobacco, alcohol, and marijuana scoring more poorly in executive function and academic performance tests [3–5]

In Chile, the latest National Study of Substances in School Population (2017) [6] has highlighted the severity of this situation. This nationwide study [6] revealed that the average age of onset of tobacco, alcohol, and marijuana use is between 13 and 14 years. These figures are concerning because scientific evidence indicates that the earlier the onset, the more devastating the impact on physical, neurological, and psychological development and the higher the risk of suffering addictive disorders in adulthood [5, 7]. Furthermore, within the month before the survey [6], 20% of the students (from 8th grade to 12th grade) reported using tobacco, about 33% reported using alcohol, and 20% reported using marijuana. Although tobacco use has been declining, alcohol use in the school population has remained relatively stable. In contrast, the annual prevalence of marijuana use has increased by 20% compared to the first survey in 2001.

In Chile, multiple substance use prevention initiatives aimed at adolescents have been evaluated and implemented. In the 1970s, the Ministries of Education and Health developed a program that was unsuccessful [8]. Over the past 30 years, the Government has promoted several initiatives, first through the National Council for Narcotics Control (CONACE) and, since 2011, through the National Service for the Prevention and Rehabilitation of Substance and Alcohol Use (SENDA). CONACE developed a “Prevention Program” consisting of various universal interventions for substance use prevention. In 2009, CONACE implemented the “Continuo Preventivo” program in schools [9]. Subsequently, in 2011, SENDA launched the “Chile Previene en la Escuela” program. Today, the “Continuo Preventivo” continues to be used, including programs between preschool and 12th grade [10]. .Another initiative is the “Familias Fuertes: Amor y Límites” program, developed by the Pan American Health Organization (PAHO). This program was implemented and evaluated in Chile through a quasi-experimental design, but six months later, adolescent involvement in risky behaviors was not reduced [11]. Despite the efforts made by the Government of Chile and several other institutions over the past few years, the results are somehow frustrating. For example, the National Plan for Substances and Alcohol 2011–2014 [12] sought to reduce the annual prevalence of marijuana and alcohol use in the school population by 15%. However, the annual prevalence of marijuana use increased dramatically from 19.5% in 2011 to 34.2% in 2015, while the annual prevalence of alcohol increased from 59.3% in 2011 to 63% in 2015 [6]. As previously noted, initiatives to prevent substance use in adolescents have been implemented but have yet to be evaluated through randomized controlled trials. For this reason, in Chile, it is necessary to evaluate programs to prevent substance use in adolescents to address this risky behavior and reduce its negative consequences.

Internationally, there are several substance use prevention programs. The Life Skills Training Program (LST) is a multi-component preventive intervention primarily intended for students to develop substance resistance skills by learning self-management strategies, establishing healthy relationships, and engaging in responsible decision-making [13]. Several RCTs have shown effectiveness in reducing tobacco, alcohol, and marijuana use among students receiving LST compared to the control group [13]. Another such program is “Project Northland” [14], a school intervention focusing on substance use prevention. It was created to be applied in rural settings characterized by problematic alcohol consumption. Results have been positive in reducing alcohol consumption and discouraging new alcohol users [14]. However, when this intervention was applied in other settings (urban, without problematic consumption), no changes in alcohol consumption were observed in adolescents [15]. The Lion’s Quest, Skills for Adolescence Program aims to develop socio-emotional competencies in students from preschool to 12th grade and includes a Substance Prevention Module [16]. This program has been evaluated in several countries, successfully reducing adolescents’ substance use while also helping them to establish healthy interpersonal relationships, increasing their motivation for learning, and reducing dropout, among other positive outcomes [16, 17]. For its part, the Seattle Social Development Project Program focuses on protective and risk factors as a way of helping students to develop interpersonal skills and better problem-solving strategies [18]. It has been evaluated through quasi-experimental studies, which have revealed less involvement in criminal acts, lower strong alcohol consumption, increased school membership, and better academic performance [19]. In a similar vein, the Raising Healthy Children Program is a multi-component preventive intervention designed to reduce risk factors and promote protective factors in student development [20]. The intervention has improved participants’ academic performance, reduced the frequency of alcohol and marijuana use (but without reducing the number of new users), and increased their school membership [18, 20, 21]. Finally, the Unplugged program [22], evaluated in seven countries (Austria, Belgium, Germany, Greece, Italy, Spain, and Sweden), is among the successful European interventions. The curriculum—which comprises 12 Unplugged sessions—is based on the theory of cognitive social influence and promotes intrapersonal skills (critical thinking versus normative beliefs) and interpersonal skills (assertiveness and skills of how to resist peer pressure), while also providing information on the different substances, in such a way as to promote good decision-making. The evaluation study showed a significant reduction in alcohol and marijuana use that persisted up to 15 months after the end of the intervention [22, 23]. This type of intervention has also allowed students to develop a better bond and a greater sense of belonging to their school [24]. A greater sense of school membership has been reported to increase involvement in healthy behaviors and reduce the likelihood of developing risky behaviors [25]. For example, a strong sense of school membership has been associated with increased motivation and academic performance [26] and greater development of health-promoting behaviors [27]. In contrast, a low level of school membership has been associated with increased negative emotions [28], suicidality [29], dropout [30], behavioral problems at school [31], and the use of substances of abuse [32].

The drawbacks or limitations of many of the programs mentioned above are: payment of a usage license and the need for a costly certified training program, a lack of validated Spanish versions for implementation in Chile or other Latin American countries, and sometimes the unwillingness of the original authors to make cultural adaptations to programs that have been tested with randomized controlled studies. The payment of the license, which only covers the use of the program without considering the costs of the materials, training, and work of teachers or facilitators, limits the viability of local implementations. Furthermore, the need to generate Spanish versions adapted to the national context represents an additional cost in terms of money and time that the authors of the programs are not always willing to cover.


### Objectives {7}

The main objective of this study is to develop a culturally appropriate version of an evidence-based substance use prevention program called Social Competence Promotion Program among Young Adolescents (SCPP-YA), adapted to the Chilean culture (Mi Mejor Plan), and to test its effectiveness among early adolescents in primary schools in Santiago, Chile.

There are two stages in this study, formative work and the study of the effectiveness of the program. The specific objectives regarding formative work are the following: (1) to translate and culturally adapt the SCPP-YA program and its Substance Use Prevention Module to the context of Chile. This work was conducted during 2019–2020; (2) to create a training course for the future facilitators. The final stage is conducting a Cluster Randomized Controlled Trial to test the effectiveness of the program. The specific objective of this stage is (1) to compare the level of self-reported substance use of 6th graders participating in the “Mi Mejor Plan” program and control schools immediately after the end of the intervention and 4 months later, controlling by baseline assessment; (2) to assess the acceptability and feasibility of the intervention in the context of schools in Chile. This study will be carried out in 2022 and 2023, presenting its protocol here.

We hypothesize that at the end of the intervention, adolescents who received the “Mi Mejor Plan” program, when compared to standard school drug prevention curricula, will have a lower 1-month of cigarette, alcohol, and marijuana use.

### Trial design {8}

This is a cluster randomized controlled trial, parallel-group type, where the “Mi Mejor Plan” program is compared to standard school prevention curricula in control schools. The standard school of drug prevention curriculum is delivered in the orientation class, henceforth “Treatment-As-Usual” (TAU) [38], and it will be used as a comparator to determine the superiority of “Mi Mejor Plan” over TAU in Chile. The patient allocation is randomized with a ratio of 1:1 (See Fig. 1).

**Fig. 1 Fig1:**
[figure not shown]
Flowchart

## Methods: Participants, interventions, and outcomes

### Study setting {9}

This trial will be performed in primary schools located in Santiago, Chile. There are 2918 schools in Greater Santiago (Region Metropolitana). After applying the inclusion criteria, the total number of eligible schools was 288. All eligible schools will be contacted, and the first 10 schools interested in participating in the study will be included in the project. These schools will be representative of the most vulnerable schools in Chile.

### Eligibility criteria {10}

#### Inclusion criteria for schools

Schools located in Santiago (Chile)Schools of Primary Education (1st grade to 8th grade)Mixed-sex schools.Schools with at least two classes in the 6th grade.Schools with at least 30 students per classSchools with vulnerability (≥50%), measured with the School Vulnerability Index – National System of Equality Allocation (IVE-SINAE). This index is the proportion of students in a given school with high vulnerability. This index considers the following socioeconomic variables to group the schools: mother’s educational level, father’s educational level, and total monthly household income, among others [39].

#### Exclusion criteria for schools

Schools implementing other substance use prevention programs similar to the contents and methodology of “Mi Mejor Plan” delivered to the same grade.

#### Inclusion criteria for participants

Attending 6th.

### Who will take informed consent? {26a}

Schools will be screened for eligibility to participate in this study based on the aforementioned criteria. After the schools have been assessed as eligible by research assistants, the principal of the selected schools will receive study information. After the school authorities accept participating in the study and sign a form, parents of students will be informed about the study and that the “Mi Mejor Plan” program will be part of the school curriculum sending information letters to their homes. Along with this information, the parent will receive the Informed Consent Form, and they need to sign it if they agree that their children participate in the study. Finally, the students will be informed about the study by research assistants and asked to sign an assent confirming their participation.

### Additional consent provisions for collection and use of participant data and biological specimens {26b}

Not applicable. No biological samples collected.

## Interventions

### Explanation for the choice of comparators {6b}

The control group receives standard school drug prevention curricula (“Treatment-As-Usual,” TAS) [38], which is not a manualized intervention. The standard curriculum includes a class called “Orientation,” where students usually participate every week in a class where they receive teaching on health promotion and substance use preventive messages. Most of the material used in these classes comes from state agencies, such as the Ministry of Education and the National Service for the Prevention and Rehabilitation of Drug and Alcohol Abuse (SENDA). Moreover, the curriculum of this class usually does not follow a manualized intervention such as “Mi Mejor Plan”; therefore, we chose the usual orientation class as a treatment-as-usual comparator to determine the superiority of “Mi Mejor Plan” over the common practice in Chile.

### Intervention description {11a}

The intervention group will receive the “Mi Mejor Plan” program. This program will be implemented during the academic year during school hours, mainly in the “Orientation” class. The program’s curriculum consists of sixteen weekly lessons delivered by a trained facilitator (member of the research team) accompanied by a school-designated teacher (who also will be trained). It is divided into two modules: (1) a social problem-solving module, consisting of 11 lessons on a method for solving social problems, and (2) a substance use prevention module, consisting of five lessons on how to apply the problem-solving method to help adolescents to prevent using substances. The research team had design-specific material for facilitators and teachers, as well as for students, to help them to complete the program. The research team will provide all the material, training, and coaching during the study. The research team will deliver the 2-day training to all facilitators, teachers, and participating school staff at the beginning of the academic year. After all the 16 lessons are completed, three booster sessions will be delivered 6–12 months later.

### Criteria for discontinuing or modifying allocated interventions {11b}

As the program is part of the school curriculum, students in the intervention group will participate in all sessions of the program. Even though they cannot leave the classroom if they do not want to participate in the sessions, they can leave the study for any reason if they wish to do so without any consequences. This means that their information and collected data will not be analyzed. On the other hand, the control group will keep its condition during the whole trial.

### Strategies to improve adherence to interventions {11c}

Adherence to the “Mi Mejor Plan” will be monitored by research assistants from the research team. After each session, teachers will fill out a survey informing students’ attendance and information about the quality of the delivery. Research assistants will be in close contact with school authorities and teachers, monitoring the progression of the program during study visits.

### Relevant concomitant care permitted or prohibited during the trial {11d}

The exclusion criterion states that schools implementing other substance use prevention programs similar to the contents and methodology of “Mi Mejor Plan,” delivered to the same grade, cannot be included in the study. This decision is based on the potential contamination of the results if another similar program is implemented in the control group. This study aims to test the effectiveness of “Mi Mejor Plan” over TAU in Chile.

### Provisions for post-trial care {30}

There is no potential harm or damage in this trial. The intervention group will receive an evidence-based intervention, and the control group will receive the usual prevention curriculum.

### Outcomes {12}

#### Primary outcome

Cigarette use in the last month, measured with the European Drug Addiction Prevention Trial Questionnaire (EU-Dap) validated in Chile [40].

#### Secondary outcomes

Alcohol use in the last month, measured with the European Drug Addiction Prevention Trial Questionnaire (EU-Dap) validated in Chile [40].Marijuana use in the last month, measured with the European Drug Addiction Prevention Trial Questionnaire (EU-Dap) validated in Chile [40].Social problem-solving, measured with The Social Problem-Solving Inventory-Revised (SPSI-RS) abbreviated 25-item version [41].Emotion regulation, measured with the Emotion Regulation Questionnaire for Children and Adolescents (ERQ-CA) [42, 43].Socio-emotional skills measured with the Strengths and Difficulties Questionnaire (SDQ) answered by students [44].Sense of school membership, measured with the Psychological Sense of School Membership Scale (PSSM), answered by students [45].

### Participant timeline {13}

Table 1 shows the participant’s timeline.

**Table 1 Tab1:**
[figure not shown]
Standard Protocol Items: Recommendations for Interventional Trials (SPIRIT) diagram

### Sample size {14}

For the sample size calculation, an absolute difference between the control group and the intervention group of 15% in the monthly cigarette consumption was adopted. Since students in the same educational institution show correlated behaviors, it is important to consider the nested data within the school for sample calculation. For substance use behaviors, the intraclass correlation coefficient (ICC) can be set at 0.01. Thus, with a difference between groups of 15%, statistical power of 80%, a significance level of 0.05, an ICC of 0.01, and a school size of about 50 students per school, four educational establishments, and 200 students per data collection branch are required. Considering a loss of 20% of the schools in the follow-up, we have included one more school in each arm, ending up of five schools and 300 students per arm.

### Recruitment {15}

The strategies for achieving adequate school enrolment to reach the target sample size will include contacting and presenting the study municipality authorities who are expected to help establish contact with school authorities. Additionally, research assistants will contact directly and inform school authorities about the study’s purpose, requirements, and duration. Our research team already has good collaborative networks with municipalities and schools in Chile.

## Assignment of interventions: allocation

Randomization will be performed once all schools are recruited. Using computer-generated randomization, schools will be randomly assigned to either group with a 1:1 allocation.

### Sequence generation {16a}

Randomization will be performed once all schools are recruited. Using computer-generated randomization, schools will be randomly assigned to either group with a 1:1 allocation.

### Concealment mechanism {16b}

After the randomization and allocation, schools will be informed by a research assistant of the group of belonging by email and confirmed by telephone. Each school will only receive their information of allocation. Additionally, this information will not be disclosed to the assessment research team (outcome evaluators) to keep the blind to the schools’ allocation.

### Implementation {16c}

An independent statistician will perform the randomization to assign to the study arms, and this statistician will give this information to a research assistant. Later, the research assistant will inform schools by email and confirm by telephone.

## Assignment of interventions: blinding

### Who will be blinded {17a}

This is a double-blinded trial, blinded to the outcome evaluators and the data analyst. Outcome evaluators will not be informed about the group of belonging and will be instructed not to ask the students or the school authorities about the school condition. A data analyst will work with the final dataset where the group condition will be masked.

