### Procedure for unblinding if needed {17b}

The design is open label with only outcome assessors and data analysts being blinded, so unblinding will not occur. On the other hand, due to the nature of the intervention, the participants will know the allocation of the school.

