## Data collection and management

### Plans for assessment and collection of outcomes {18a}

Data will be retrieved from:The European Drug Addiction Prevention Trial Questionnaire (EU-Dap), a self-reported questionnaire, aims to screen substance use and assess risk and protective factors among adolescents. It has 45 multi-item questions and focuses especially on tobacco, alcohol, and marijuana use. The EU-Dap instrument was developed by the research team of the Unplugged program in Europe. It was used to evaluate the Unplugged trial project, which took place between 2003 and 2005 in seven countries in Europe. In the Chilean validation study, all subscales had acceptable internal reliability (omega > 0.65) [40]. The original form of the questionnaire can be found at http://www.eudap.net.The Social Problem-Solving Inventory-Revised (SPSI-RS) consists of five scales that evaluate two dimensions of Problem Orientation (Positive Problem Orientation and Negative Problem Orientation) and three Troubleshooting styles (Rational Troubleshooting Style, Impulsive/Careless Style, and Avoidance Style). The abbreviated 25-item version [41] will be used in this study; in this shorter instrument, each scale has five items, with the full scale comprising 25 items. The inventory must be answered as a 5-choice Likert-like scale, in which the subjects indicate to what extent the proposed coping strategy applies to their characteristic way of dealing with the problems of daily life (0- it does not apply at all to me, 1- it applies slightly to me, 2- it applies moderately to me, 3- it applies a lot to me, and 4- it applies extremely to me). It has acceptable internal reliability (Cronbach alpha > 0.75) [41].The Emotion Regulation Questionnaire for Children and Adolescents (ERQ-CA). Emotional regulation is defined as the ability to control and manage one’s feelings and emotions and appears to be an important factor in social adjustment. The questionnaire consists of 10 items. The answers on the questionnaire have a five-point Likert scale quantifying the agreement to the behavior described (1 = strongly disagree, 2 = disagree, 3 = half and half, 4 = agree, 5 = strongly agree). This instrument provides scores on two uncorrelated scales: Cognitive Reappraisal (6 items) that consists of redefining a potential emotion-eliciting situation in a way that its emotional impact is changed; and Expressive Suppression (4 items), encompassing a style that consists of the inhibition of ongoing emotion expressive behavior. It has acceptable internal reliability (Cronbach alpha > 0.75) [43].The Strengths and Difficulties Questionnaire (SDQ). This is a questionnaire of 25 mental health items for a population of 4 to 17 years. It evaluates positive and negative psychological aspects, grouped into five sub-scales: (1) emotional symptoms, (2) behavioral problems, (3) attention and hyperactivity problems, (4) social relationship problems, and (5) pro-social behavior. The first four sub-scales refer to difficulties, while the last sub-scale refers to strengths. Several studies have shown that the instrument has good psychometric properties; our research team has already conducted a validation study in early adolescents in Chile [44]. This validation study confirmed the 5-dimensional structure of the instrument while also showing that its internal reliability ranges from 0.53 to 0.71 for the self-reporting version.The Psychological Sense of School Membership Scale (PSSM). The sense of school membership refers to the student’s perceptions of the respect and acceptance that teachers and other students show them and their sense of belonging. It is a scale that our research team has already validated in Chile in early adolescents. This scale has 13 items (Chilean version) and is a single dimension, with high internal reliability (Cronbach’s alpha 0.92) [45].

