## Oversight and monitoring

### Composition of the coordinating center and trial steering committee {5d}

This is a monocenter study designed, performed, and coordinated in Universidad de los Andes, Chile. Daily support for the trial is provided by the principal investigator, who supervises the trial. Additionally, a data manager organizes data collection and assures data quality. The study coordinator will help with the trial registration and coordinate study visits and reports. Study research assistants will help identify potential participating schools, collect informed consents, ensure follow-up according to protocol, and resolve doubts from school staff or participants.

The study team will meet weekly during the whole duration of the study. There is no trial steering committee or stakeholder and public involvement group. The Ethical Scientific Committee of the Universidad de los Andes will check the presence and completeness of the investigation.

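### The double-blind label conflicts with an open-label design whose outcomes are self-reported by unmasked pupils, and the parent letter as described is either arm-revealing or untrue in control schools

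*Protocol article*

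**What the plan says.** **Label.** Section {17a}, Who will be blinded: "This is a double-blinded trial, blinded to the outcome evaluators and the data analyst". Section {17b}, Procedure for unblinding: "The design is open label with only outcome assessors and data analysts being blinded, so unblinding will not occur". The same section adds that "due to the nature of the intervention, the participants will know the allocation of the school".

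**Outcome.** The primary outcome is last-month cigarette use on the EU-Dap. Section {18a} describes that instrument as "a self-reported questionnaire, aims to screen substance use", among other aims.

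**Parent letter.** Section {26a} says that, once the school has accepted, parents are told about the study and that the Mi Mejor Plan "program will be part of the school curriculum sending information letters to their homes". The consent form travels with this information and must be signed. Pupil assent follows.

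**Timing.** The allocation section, repeated under {16a}, says: "Randomization will be performed once all schools are recruited". Section {16b} says schools are told their arm after randomisation. The visible text does not place parental consent, pupil assent or the baseline questionnaire before or after that notice.

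**The concern.** Two separate matters are at stake.

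The first is what the blinding description promises. A reader who meets only {17a} would take the trial to have a protection that it lacks. Here the pupil produces the outcome, and the pupil knows the arm. Pupils who have been taught to avoid substances may be less willing to admit smoking, whoever hands out the form. That would look like a programme effect.

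The second is who enters the trial. Schools are randomised, but pupils join through parental consent and their own assent. If parents or pupils know the arm when they decide, the kinds of pupils enrolled can differ between arms, and randomising schools does not correct that. The letter as described would tell intervention-school parents their arm if it went out after allocation.

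**Working it through.** The protocol gives no figure to reproduce on this point, so most of the check sets its statements side by side.

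**1. Label.** {17a} says double-blinded and names outcome evaluators and the data analyst. {17b} says open label and names the same two groups. The list of masked people is consistent. The two labels are not, and the open-label one fits the list, because participants are stated to know the allocation.

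**2. What the masking covers.** The primary outcome comes from the EU-Dap, which the pupil completes. Masking the collector and the analyst covers administration and analysis. It does not cover the answer itself.

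**3. The letter.** Its described content is that the programme will be part of the curriculum. Control schools keep the usual orientation class.

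| When the letter goes out | Intervention schools | Control schools |
|---|---|---|
| After allocation is disclosed | True, and reveals the arm before consent | Untrue, unless a different letter is used |
| Before allocation | Arm not yet known | Proves untrue |

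Under neither timing does the described text suit all schools. Only the first timing opens a route to selective consent by arm.

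**4. Order of events.** Randomisation is tied to school recruitment only. This allows pupil consent and baseline to come either before or after it. Fig. 1 and Table 1 may show the order, but they are not visible here.

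**5. Illustration of reporting bias.** Let *p* be the true smoking rate in both arms (no effect) and *u* the share of intervention-arm smokers who deny use. **Both are assumptions**; the documents give neither. Reported use in the intervention arm is q = p(1 − u), and OR = [q/(1 − q)] / [p/(1 − p)].

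Example with p = 0.10 and u = 0.20: q = 0.10 × 0.80 = 0.08, and OR = (0.08/0.92)/(0.10/0.90) = 0.78.

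| p | u = 10% | u = 20% | u = 30% | u = 50% |
|---|---|---|---|---|
| 5% | 0.90 | 0.79 | 0.69 | 0.49 |
| 10% | 0.89 | 0.78 | 0.68 | 0.47 |
| 20% | 0.88 | 0.76 | 0.65 | 0.44 |

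To see how often this would reach significance, take the planned 300 pupils and five schools per arm. That is 300/5 = 60 pupils per school. With the protocol's ICC of 0.01, the design effect is 1 + 59 × 0.01 = 1.59, and the effective size is 300/1.59 ≈ 189 per arm. A two-proportion normal approximation, two-sided 0.05, gives these chances of a significant result favouring the programme:

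- p = 10%, u = 30%: about 18%
- p = 20%, u = 30%: about 34%
- whole grid: from about 4% (p = 5%, u = 10%) to about 78% (p = 20%, u = 50%)

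With no bias the nominal figure is 0.05/2 = 2.5%. The approximation assumes no losses and ignores the small number of schools, so these figures are only indicative.

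**The case against.** The best defence has four parts.

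- **The label conflict is editorial.** Each section says exactly who is masked, and nobody who reads both would think pupils are masked. This stands as to roles. It does not rescue the word double-blinded, which claims more than the design delivers.
- **Unmasked self-report cannot be avoided in a classroom programme, and the protocol discloses both facts.** This stands. Correcting the label does not reduce reporting bias; it makes the description accurate and lets readers weigh the result. The odds ratios above show what such bias could do, not what the correction would prevent.
- **The order of consent and allocation may be in the flowchart or participant timeline, and the letter is summarised, not reproduced.** This stands. A reader might infer that parents consent knowing their arm and that enrolment will therefore be biased. The documents do not support that: the order is unstated in the visible text, and a letter sent before randomisation cannot produce selective consent by arm. What remains is that the described content does not fit control schools at either timing.
- **Assessor masking is already provided for.** A reader might also infer that it is compromised, because research assistants notify schools, monitor sessions and take part in follow-up; section {5d} says "Study research assistants will help identify potential participating schools, collect informed consents, ensure follow-up according to protocol". That inference does not hold. {16b} withholds allocation from the outcome evaluators, {17a} tells them not to ask about it, and nothing says that the same individuals fill these roles.

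**Conclusion.** The point holds in three limited parts.

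1. The double-blinded label in {17a} is contradicted by {17b} and should go. This is certain from the text.
2. Masking the questionnaire collectors does not mask a self-reported primary outcome. This follows directly from {17b} and {18a}. The possible size rests on two assumed inputs: over smoking rates of 5–20% and denial of 10–50%, the spurious odds ratio runs from about 0.90 to 0.44. It is a limit on interpretation that the design cannot remove.
3. The parent letter as described needs correcting whenever it is sent. Selective enrolment is a risk left open by the visible text, not a demonstrated flaw. The documents offer no basis for sizing it.

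The changes are worth making because they are cheap, and because the letter and the sequence of steps bear on whether the enrolled pupils are comparable between arms.

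**What to change.** - **Section {17a}:** replace double-blinded with *open label; questionnaire collectors and data analyst masked*. State that the self-reported outcomes come from pupils who know their school's arm, and that this limits interpretation.
- **Section {26a}:** use one parent letter for all schools that does not indicate the arm, for instance by saying that schools will be assigned by chance to the programme or to the usual orientation curriculum.
- **Allocation section and {16a}:** state that parental consent, pupil assent and the baseline questionnaire are completed in every school before any school is told its arm. If Fig. 1 or Table 1 already shows this order, repeat it in the text.
- **Any illustration of reporting bias:** present both the smoking rate and the concealment rate as assumptions, with a range.

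The cost is wording, letter text and sequencing, with no extra staff. The one downside is a short delay in telling schools their arm. This must fit with the staff training, which {11a} places at the start of the academic year, and with participant recruitment, which the trial status section expects to finish at the end of April 2022.
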